##### Hand-grip strength

Participant’s hand-grip strength will be measured on each hand using a hydraulic hand dynamometer (Jamar Hand Dynamometer, USA) which can measure isometric grip force up to 90 kg. This device has been found to have good reliability and reproducibility [96]. The device will be calibrated at the start of each measurement day. Each participant will be asked to sit upright on a chair with their forearm on the armrest and then grasp the handle of the device in their right hand. Participants are required to maintain a 90° angle in their elbow adjacent to their side so that their thumb faces upwards while squeezing the handle as strongly as possible for approximately 3 s. The same protocol will be applied to the left hand. The measure will be repeated three times on each hand. Standardised encouragement will be provided during the assessment. The average values of the two hands will be used.

##### Total PA behaviour

PA behaviour will be assessed at baseline and in the last week of the 12-week intervention and 3-month follow-up period using the Axivity AX3 wrist-worn triaxial accelerometer (Axivity, Newcastle, UK). Participants will wear the waterproof device for seven consecutive days, for 24 h a day, on their nondominant wrist. Raw acceleration files (.cwa), with a sampling frequency of 100 Hz, will be downloaded using the OmGui Software (Open Movement, Newcastle, UK) and processed in R software using the software package GGIR [97]. Specifically, the package will convert raw accelerations (*x*-, *y*- and *z*-axes) to magnitudes of dynamic acceleration (expressed as Euclidean Norm Minus One, ENMO) averaged over 1-s epochs in milli-gravitational units (m*g*). Time accumulated in MVPA per week will be calculated and expressed in milli-gravitational units (m*g*). Thresholds of approximately 100 mg and 400 mg will be used to represent moderate and vigorous intensity activities respectively [98]. Participants will be required to have at least three valid days of data according to standard GGIR software package processing to be included in the analysis. Non-wear time will be defined as consecutive stationary episodes lasting for at least 60 min. The outputs will be processed to provide time spent in MVPA per week. These monitors have been validated to assess PA energy expenditure [99].

##### Travel behaviour (changes in transportation modes and trip purpose)

Spatial location data will be collected using a personal GPS receiver (Qstarz International Co. Ltd., Taiwan) to describe participants travel behaviour at baseline (i.e. before obtaining the e-bike), in the final week of the intervention and in the final week of the 3-month follow-up. Participants will be asked to wear the GPS during waking hours and recharge it at night. The device can be worn around the waist or in a pocket as desired. GPS time and positional data will be used to identify journey start and finish times and estimate velocities. In addition, participants will also be asked to complete a 7-day travel diary over the same period as GPS monitoring. The travel diary is adapted from Neves and Brand [100] and will ask participants to record every journey made over the 7-day period. Participants will be asked to classify the journey under one of five categories: commuting for work, commuting for education, travel for business, shopping or personal business and social visits or leisure activities. For each journey, participants will be asked to report the travel mode, start and end time and start and end location. The information from the travel diary will be used to (a) capture contextual data related to trips (e.g. trip purpose), (b) validate the GPS and (c) provide an alternative source of data in case the GPS fails, is not turned on, or the battery dies. This information will allow us to determine the total distance travelled by active transportation (i.e. walking or cycling) compared with motorised transportation and to compare different modes of active transportation.

##### E-cycling behaviour and intensity

E-cycling behaviour will be measured during the intervention and follow-up period in the intervention group using a Fitbit Charge 5 watch. The Fitbit Charge 5 is an integrated GPS and heart rate monitoring watch which can store up to 7 days of activity tracking. Participants will have the option to pair the device with a smart phone using Bluetooth. If Bluetooth pairing is used, then activity data will be automatically uploaded to the Fitbit website. If the participant chooses not to pair the device, then the data will be downloaded each week by the researcher. The watch will need charging during the loan period; all charging cables and instructions will be provided. Outcomes derived from the watch will include the frequency and duration of e-cycling journeys and intensity of activity associated with e-cycling based on heart rate data. Wrist-worn consumer devices, including the Fitbit, have been reported to have acceptable accuracy for the measurement of heart rate in research settings and are more ecologically valid than research devices [101, 102]. Average journey speed will also be derived. The purpose of journeys will be derived through land use maps and using home and work postcodes. Participants will be provided with a paper logbook should they not wish to use the watch. The logbook will ask participants to record each e-cycling trip, the duration, the start and end location and the purpose. An inbuilt odometer on each bike will also collect data on the total number of kilometres ridden during the trial in case the watch or logbook is not used. Participants will use the watch or complete the logbook for the intervention period and for the 3-month follow-up period. After this time, the watches will be returned to the researcher, and data from the Fitbit device and/or online website will be downloaded to a University of Bristol computer and securely stored. After all data is downloaded, it will be deleted from the Fitbit website and the device itself. Participants will not be required to enter their name, address or email when setting up the Fitbit device; all devices will be connected to a University of Bristol email address, and the participant’s ID will be used in place of their name. However, due to the nature of GPS tracking, participant’s start and end points of journeys will be identifiable from the GPS tracks. This will be made clear to the participants in the information sheet and in the consent form.

### Data analysis

#### Quantitative analysis

The primary outcomes of this pilot trial include recruitment and consent rates, retention and adherence to study procedures and data provision. Analysis of these data will be descriptive, expressed as frequencies and percentages. Any adverse events will be described appropriately. Characteristics of the sample will be summarised using descriptive statistics (means and standard deviations, medians and interquartile ranges or frequencies and percentages as appropriate). Descriptive comparisons of these data will be made between the intervention and the waitlist control. Evidence of promise of the intervention (i.e. whether the intervention can lead to changes in outcomes measures) will be examined using comparison of change scores between conditions for all outcome measures (except e-cycling during the intervention). See Table 3 for a description of the outcome measures and proposed analysis plan for each outcome. Effect estimates will be presented with 95% confidence intervals reported; *p*-values will not be considered as the study is not powered to detect effectiveness. All analysis will be undertaken in Stata v17.

**Table 3 Tab3:** List of CRANK research questions, associated outcomes, data collection tools, time point measurements and analysis plan

Research question	Outcome	Data collection method/tool	Time point of measurement				Analysis plan
			Baseline (T0)	During intervention	Post (T1)	3-month FU (T2)	
1. Can individuals with prostate/breast cancer be recruited into an e-cycling trial?	• No. of individuals in clinic; no. of meeting eligibility criteria; no. of express interest in participating • Reasons for not wanting to participate in the study • No. of individuals that consent to be part of the study	Study records	X				Frequencies and percentages
2. Are participants’ willing to be randomised, do they remain in the study and adhere to the intervention and data collection methods and what are the rates of harmful events?	• No. of participants retained in study following randomisation • No. of individuals that complete follow-up testing • No. of participants that attend each of the intervention sessions and data collection sessions • No. of harmful events	Study records		X			Frequencies and percentages
3. Can the intervention be implemented as intended?	• No. of training sessions attended by participants and additional contact with instructors • Extent to which intervention content is completed as planned • No. of and extent of adaptations	Intervention checklists		X			Frequencies and percentages
4. Are the intervention and study procedures acceptable to participants, instructors and clinical team?	• Acceptability of recruitment strategy to clinical team • Acceptability of intervention to participants • Acceptability of study procedures to participants • Acceptability of intervention delivery to instructors	Semi-structured interviews			X		Thematic analysis based on research question
5. What are participants experiences of e-cycling?	• Experiences of e-cycling • Participant’s barriers and facilitators to e-cycling	Semi-structured interviews			X		Thematic analysis based on research question
6. What is the potential effect of the intervention on a range of individual health and behavioural outcomes?	• Weight, BMI and waist circumference	Tanita digital scales, SECA 700, non-stretch take	X		X	X	Comparison of change scores between conditions Reporting of effect estimates with 95% CI
	• Metabolic markers (fasting glucose, insulin, insulin resistance, lipid profile, IGF-I, IGF-II, IGFBP-2, IGFBP-3, PSA^a^)	8-mL blood sample	X		X		
	• General health-related quality of life	EuroQol-5 dimension-5 level	X		X	X	
	• Cancer-specific quality of life	EORTC QLQ-C30 EORTC PR-25^a^ EORTC BR-45^b^	X		X	X	
	• Urinary health^a^	ICIQ-MLUTS	X		X	X	
	• Erectile dysfunction^a^	International Index of Erectile Function	X		X	X	
	• Fatigue	FACIT-F	X		X	X	
	• Self-efficacy for coping with cancer	Cancer Behaviour Inventory — Brief	X		X	X	
	• Cardiorespiratory fitness	Maximum oxygen uptake using cycle ergometer	X		X	X	
	• Hand grip strength	Hydraulic hand dynamometer	X		X	X	
	• Total physical activity (time spent in moderate-to-vigorous physical activity)	Axivity AX3	X		X	X	Comparison of change scores between conditions
	• Travel behaviour • No. of trips • Transport mode (walking, cycling, e-cycling, car, bus, train) • Trip purpose	QStarz GPS and travel diary	X		X	X	Mean and SD
	• E-cycling behaviour and intensity: no. of journeys, duration, distance travelled, purpose of use	Bike odometer, Fitbit Charge 5 GPS watch, logbook		X			Mean and SD

^a^CRANK-P only, ^b^CRANK-B only

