## Methods

### Study design and setting

The proposed trials are single-centre, stratified, parallel, two-arm pilot randomised control trials, whereby individuals with PCa (*CRANK-P*) or BC (*CRANK-B*) will be randomly assigned to either an e-cycling intervention or a standard-care waitlist control. Forty individuals will be recruited for each trial and randomised in a 1:1 allocation ratio to the two study arms. The trials will be conducted in the city of Bristol, England. Recruitment began in June 2022. Measures will be collected predominantly at baseline (time 0 (T0)), immediately following the intervention period (T1) and at 3-month follow-up (T2). In addition, data will be collected in the final week of the e-cycling intervention and follow-up period (PA and travel behaviour) and throughout the intervention and follow-up period (e-cycling time and distance). Figure 1 shows the study flow diagram for the two trials. Reporting of this protocol is according to the SPIRIT checklist (Additional file 1). CRANK-P has been approved by the NHS Health Research Authority Dulwich Research Ethics Committee (REC: 22/LO/0036), and CRANK-B has been approved by the Nottingham Research Ethics Committee (REC: 22/EM/0010). Both trials are sponsored by the University of Bristol. Any amendments to the protocol will be authorised by the sponsor and submitted to the appropriate REC and HRA for approval.

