### Sample size

The study will aim to recruit and randomise 40 individuals for each pilot RCT. This sample size is based on recommendations for pilot studies which aim to provide an estimation of a standard deviation for use in the sample size calculation to inform a larger randomised controlled trial [61, 62], as well as the availability of e-bikes. There are no explicit targets regarding the number of individuals to be recruited or screened as we are investigating the feasibility of recruitment from the clinical setting. Based on recruitment rates in a similar population (individuals recovering from colorectal cancer) and recruitment occurring in a clinical setting, we anticipate a recruitment rate of approximately 20% [63]. Recruitment and screening will close when 20 participants have been randomised to each of the two study arms. Based on a previous pilot randomised controlled trial of e-cycling among individuals with type 2 diabetes mellitus, a retention rate of approximately 80% is anticipated [58].

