### Allocation, randomisation and blinding

Randomisation will occur after consent is obtained and baseline data (T0) has been collected. For each pilot RCT, 40 individuals will be randomly assigned to either the e-cycling intervention or waitlist control in a 1:1 allocation ratio. For CRANK-P, individuals will be stratified based on cancer treatment received prior to randomisation. For CRANK-B, individuals will be stratified based on stage of cancer treatment prior to randomisation. Permuted blocks of random size will be used. A random allocation sequence will be generated by an independent statistician using R v4.1.2, package blockrand (v1.5). The randomisation sequence will be accessible through a password-protected Excel file. The researcher will access the Excel file and allocate the participant to either condition in the order issued in the sequence. Researchers will be aware of the group allocation. Participants will be informed of the group allocation via telephone by a member of the research team. Blinding of intervention allocation will not be possible for any participant involved in the trial or the researchers.

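### Promise is estimated by a plain comparison of change scores; adjusting for baseline and stratum would usually give narrower intervals at no cost, and the travel row of Table 3 needs reconciling with the text

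*Protocol article*

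**What the plan says.** The Quantitative analysis section of the protocol article states that evidence of promise "will be examined using comparison of change scores between conditions for all outcome measures (except e-cycling during the intervention". Table 3, under research question 6, repeats this as the analysis for the health and physical activity outcomes: "Comparison of change scores between conditions". On reporting, the text adds: "Effect estimates will be presented with 95% confidence intervals reported". It sets p-values aside: "values will not be considered as the study is not powered to detect effectiveness".

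The Outcome measures section has outcomes measured at T0 unless stated otherwise, so a baseline value is at hand. Randomisation is stratified in both trials. The Allocation section says: "For CRANK-P, individuals will be stratified based on cancer treatment received prior to randomisation"; CRANK-B is stratified by treatment stage. No section names the baseline value or the stratum as a covariate, and none rules them out.

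For travel behaviour, measured at baseline and at both later time points, Table 3 gives only a mean and SD.

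**The concern.** Subtracting the baseline amounts to assuming that its coefficient is exactly 1. When the correlation between baseline and follow-up is below 1, that over-corrects: an arm that starts high by chance is expected to fall back, and the change score credits that fall to the arm. ANCOVA estimates the coefficient from the data. A prognostic stratum left out of the model leaves its variation in the residual, so the reported interval is wider than the design warrants.

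Precision is scarce in trials of this size, and the results are meant to help plan a larger one. The Sample size section says: "This sample size is based on recommendations for pilot studies which aim to provide an estimation of a standard deviation". The SD carried forward depends on the analysis intended for the definitive trial.

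Separately, the text exempts only e-cycling during the intervention from the between-arm comparison, while the travel row of Table 3 contains no such comparison.

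**Working it through.** **Inputs from the protocol article.** Size and allocation: "Forty individuals will be recruited for each trial and randomised in a 1:1 allocation ratio to the two study arms" (Study design and setting), and "Recruitment and screening will close when 20 participants have been randomised to each of the two study arms" (Sample size). The Sample size section expects about 80% retention. So 40/2 = 20 per arm randomised, and 0.8 × 20 = 16 per arm (32 per trial) completing. These figures agree with each other. The document states no SD, correlation, effect size or interval width, so there is no precision figure to reproduce.

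**Assumptions.** Equal SD at both visits (results in SD units) and correlation r from 0.3 to 0.95. The document gives no value for r.

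**Interval half-widths, n per arm.**

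- Change score: t(0.975, 2n−2) × √[2(1−r)] × √(2/n)
- ANCOVA: t(0.975, 2n−3) × √(1−r²) × √(2/n) × √[1 + 1/(2n−4)]

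At n = 16 and r = 0.5, the change score gives 2.042 × 1 × 0.3536 = 0.722. ANCOVA gives 2.045 × 0.866 × 0.3536 × 1.018 = 0.637. The ratio is 0.883, or 12% narrower.

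**Shift from chance imbalance.** The standard error of the baseline difference is √(2/16) = 0.354 SD. Given a baseline difference D, the change-score estimate moves by (1−r) × D in the opposite direction. At r = 0.5 and D = 0.354 this is 0.177 SD.

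| r | Change score half-width | ANCOVA half-width | Ratio | Shift per one-SE imbalance |
|---|---|---|---|---|
| 0.3 | 0.854 | 0.702 | 0.822 | 0.247 |
| 0.5 | 0.722 | 0.637 | 0.883 | 0.177 |
| 0.7 | 0.559 | 0.526 | 0.940 | 0.106 |
| 0.8 | 0.457 | 0.442 | 0.967 | 0.071 |
| 0.9 | 0.323 | 0.321 | 0.993 | 0.035 |
| 0.95 | 0.228 | 0.230 | 1.006 | 0.018 |

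With all 20 per arm the picture is the same: ratios 0.879, 0.936, 0.989 and 1.002 at r = 0.5, 0.7, 0.9 and 0.95. A one-SE imbalance is then 0.316 SD, and the shifts at 0.5 and 0.7 are 0.158 and 0.095 SD.

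**Stratum.** A simulation used 3,000 runs per setting, 16 per arm and two balanced strata that differ at follow-up by 0 or 0.5 SD (an assumption). Ratios of mean half-width to that of the change score:

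| r | Stratum difference | Baseline only | Baseline and stratum |
|---|---|---|---|
| 0.5 | 0 | 0.882 | 0.884 |
| 0.5 | 0.5 SD | 0.894 | 0.860 |
| 0.9 | 0 | 0.993 | 0.995 |
| 0.9 | 0.5 SD | 1.001 | 0.860 |

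A non-prognostic stratum brings no gain. A prognostic one helps even where baseline adjustment does not. Because the strata are balanced by design here, the gain lies in the reported interval: at r = 0.5 with a 0.5 SD difference, the spread of the estimate is 0.305 SD with or without the stratum term. The mean of every estimator was within about 0.01 SD of the true value of zero.

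**Planning.** In large samples, the change-score variance divided by the ANCOVA residual variance is 2/(1+r): 2/1.5 = 1.33 at r = 0.5 and 2/1.7 = 1.18 at r = 0.7. A definitive trial sized on the SD of change but analysed by ANCOVA would be about 33% or 18% larger than needed. The article does not say which SD will be used.

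**The case against.** The plan nowhere calls the comparison unadjusted. Regressing change on arm, baseline and stratum is also a comparison of change scores and yields the same arm effect as ANCOVA, and covariates are often left to an analysis plan, which is not shown. This stands in part: the absence of covariates is read from silence. But the comparison named in the text and in Table 3, taken as written, contains no such term, and naming one would settle the matter.

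The consequence is limited. The Abstract describes the analyses as descriptive, the primary outcomes are feasibility rates, and no progression decision is tied to these estimates. That stands and sets the weight of the point.

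A reader might infer four stronger claims, which are not supported:

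- That the baseline is ignored. It is not; a change score subtracts it.
- That every interval is too wide. At r of 0.9 or above, plausible (as an assumption) for weight or BMI, baseline adjustment gains 1% or less and can lose slightly.
- That the estimates are biased. The shift is conditional on a given imbalance and averages to zero over randomisations.
- That the CRANK-P strata must diverge because newly diagnosed men begin treatment between T0 and T1 and post-treatment men do not. No section says this. The Recruitment section has future treatment discussed at the post-treatment appointment, and the Allocation section does not equate the stratum with the two recruitment points.

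On travel, the text sends the reader to Table 3 for each outcome's plan, and the stated purpose of the GPS data is descriptive. That makes the mismatch minor but does not remove it.

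**Conclusion.** The point holds as an improvement that needs no new data. The named comparison is valid on average but usually less precise than one adjusted for baseline. The gain in interval width at 16 per arm is worthwhile for outcomes with low or moderate correlation and vanishes for very stable ones. Chance imbalances of the size tabulated are ordinary in samples this small, and adjustment removes their effect on the estimate. The case for the stratum term depends on its being prognostic, which the documents neither show nor exclude. All sizes rest on the assumed correlations, equal SDs at the two visits and the retention that the protocol anticipates. The mismatch between the text and the travel row of Table 3 is real, and is a matter of wording.

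**What to change.** For continuous outcomes, replace the comparison of change scores in the Quantitative analysis section and Table 3 with: follow-up value regressed on arm, baseline value and stratification factor at each time point, reporting the adjusted mean difference with 95% CI. A joint T1 and T2 model is an option only for outcomes measured at both; Table 3 schedules the metabolic markers at T0 and T1 only. Because the number of strata is not stated, say in advance how sparse strata will be combined.

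Report the residual SD and the baseline to follow-up correlation for each outcome, so that the definitive trial can be sized for the analysis it will use.

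For travel, make the text and Table 3 agree. Either give trip counts and distances the same adjusted comparison, or add travel to the exemption in the text. In either case report mode and purpose as proportions, since a mean and SD does not describe categories.

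The cost is a change of analysis wording, with no new data, visits or participants.

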### Study aims and objectives

The *primary* aim of this study is to test the feasibility of conducting two pilot randomised controlled e-cycling interventions among individuals with PCa (*CRANK-P*) and BC (*CRANK-B*). Two pilot RCTs will be conducted because these different clinical populations have different recruitment and treatment pathways. However, the primary aim of the two trials is the same and will be addressed by answering the following questions:Can individuals with PCa/BC be recruited to an e-cycling trial?Are participants’ willing to be randomised, do they remain in the study and adhere to the intervention and data collection methods, and what are the rates of harmful events?Can the intervention be implemented as intended?Are the intervention and study procedures acceptable to participants, instructors and the clinical team?What are participants’ experiences of e-cycling?

While the pilot RCTs will be insufficiently powered to statistically examine the effectiveness of the intervention on outcomes, they provide an opportunity to investigate the potential promise of the intervention. As such, the *secondary* aim is to examine the association between the intervention and outcome measures to determine intervention promise. To address this aim, the following question will be answered:6.What is the potential effect of the intervention on a range of individual health and behavioural outcomes?

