#### Feasibility and acceptability

To assess feasibility of recruitment, the number of individuals that attend the clinics and the number that are deemed eligible will be recorded. Recruitment rates, consent rates and willingness to be randomised will be recorded. Retention rates will be determined based on the number of individuals that complete the intervention, post testing, and follow-up measures. Adherence rates to study procedures will be recorded.

The acceptability of the recruitment methods and individuals’ receptiveness to the study will be explored through semi-structured one-to-one interviews with the clinical care team. The acceptability of the study procedures, including data collection methods, and the intervention will be explored through semi-structured one-to-one interviews of all study participants and instructors. These interviews will be conducted by a member of the research team. Interview questions for instructors will focus on factors that impact intervention delivery, including intervention content, facilities, time and burden. Interview questions for participants will focus on thoughts and feelings regarding participation in the intervention and data collection processes. The research team will track the costs and resources required for running the trial. Life Cycle will track the staff costing of intervention delivery and from the maintenance service. This information will be shared with the University of Bristol research team.

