#### Intervention fidelity

The degree to which the intervention was delivered and received as intended (implementation) will be evaluated following criteria proposed by Lambert and colleagues [71]. Specifically, all instructors delivering the intervention will undertake training which will include information on the benefits of PA for individuals with cancer and training on how to engage in discussions around personal health. A separate training session focused on the theoretical bases of the intervention, the principles of motivational interviewing and the specific intervention content will also be delivered. Training will include role plays with supervised feedback which will be documented. Following the training, instructor’s intervention delivery will be observed by a member of the research team and observation checklists completed to record instructors’ delivery of the intervention content, receipt of the intervention by participants and enactment of the behavioural skills. Throughout the intervention, instructors will be asked to complete checklists to ascertain what skills training and discussions occurred during each session.

Intervention intensity, recorded by instructors, will be determined through recording of the number of intervention sessions attended by participants as well as the volume of email and telephone contact between instructors and participants. At the end of the study, information on attendance to intervention sessions and tasks completed within each session will be passed from Life Cycle to the research team. Participant’s ID, and not names, will be recorded on intervention documentation.

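### Adherence to the intervention is a primary question, but its only indicator in Table 3 is session attendance; e-bike use sits under a secondary question as mean and SD, which cannot show how many participants did not ride or stopped

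*Protocol article*

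**What the plan says.** Study aims and objectives makes adherence to the intervention part of the primary aim. Question 2 asks of participants: "do they remain in the study and adhere to the intervention and data collection methods".

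The indicators are set out in these places:

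- **Table 3, question 2.** Besides retention, completed follow-up testing and harmful events, the table lists "No. of participants that attend each of the intervention sessions and data collection sessions", reported as frequencies and percentages from study records.
- **Quantitative analysis, primary outcomes.** Among the primary outcomes named are "retention and adherence to study procedures and data provision". Adherence to the intervention is not named.
- **Feasibility and acceptability.** "Adherence rates to study procedures will be recorded". For retention: "Retention rates will be determined based on the number of individuals that complete the intervention, post testing, and follow-up measures". Completing the intervention is given no riding component.
- **Intervention fidelity.** Intensity is determined from "recording of the number of intervention sessions attended by participants", together with email and telephone contact.
- **Table 3, question 6.** E-bike use appears as "E-cycling behaviour and intensity: no. of journeys, duration, distance travelled, purpose of use", with mean and SD as the analysis. Question 6 serves the secondary aim, of which the article says the "aim is to examine the association between the intervention and outcome measures to determine intervention promise".

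Under E-bike loan, participants ride as they wish and no amount is set. Under E-cycling behaviour and intensity, riding is captured by watch or logbook, with the bike's odometer as a fallback that gives total kilometres.

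**The concern.** After training, the main thing a participant receives is a bike for 12 weeks. Whether it gets ridden is central to whether the intervention was taken up. A count of sessions attended does not measure that: someone can keep the week 4 and week 8 appointments and leave the bike unused in between.

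The data that would answer the question are collected, but they are assigned to a different, secondary question and reduced to a mean and SD. Quantitative analysis also excludes e-cycling during the intervention from the between-arm comparison. In Table 3 it therefore describes uptake in one arm and does not estimate an effect, so question 2 is its more natural place.

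At stake is how informative the answer to a primary feasibility question will be. The pilot is meant to inform the design of a definitive trial, and its designers would want to know what share of participants rode at all and what share were still riding near the end of the loan.

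**Working it through.** The document states no adherence figure, so there is nothing to reproduce. The check compares the question with its indicators and then tests what the planned summary can show.

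**Step 1. Match question to indicator.** The four items under question 2 are retention, follow-up testing, session attendance and harmful events. Only attendance relates to intervention adherence, and it contains no riding. Sessions attended are also counted under question 3 (implementation), so question 2 adds little of its own on uptake. Attendance misleads in the other direction too: under E-bike training, the need for session 2 is agreed between instructor and participant, so missing it lowers the count without showing poor adherence.

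**Step 2. Size of the group.** 40 per trial at 1:1 gives 40 / 2 = 20 in the intervention arm (Sample size). One participant is 1 / 20 = 5 percentage points.

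**Step 3. Can mean and SD show non-riders?** Take two constructed arms of 20. The distances are assumed, for illustration only.

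- Arm A: 10 people at 0 km, 10 at 60 km. Mean = (10 × 0 + 10 × 60) / 20 = 30.0. Sum of squares = 20 × 30² = 18,000. SD = √(18,000 / 19) = 30.8. Non-riders: 10.
- Arm B: 16 people at 15 km, 4 at 90 km. Mean = (16 × 15 + 4 × 90) / 20 = 30.0. Sum of squares = 16 × 15² + 4 × 60² = 3,600 + 14,400 = 18,000. SD = √(18,000 / 19) = 30.8. Non-riders: 0.

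Mean and SD are identical, yet half never rode in A and everyone rode in B. The other summaries separate them. The median is 30 in A (midpoint of 0 and 60) and 15 in B; the range is 0 to 60 in A and 15 to 90 in B. Attendance could be 20/20 in both.

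**Step 4. What a proportion would look like.** Exact (Clopper-Pearson) 95% intervals, with assumed counts of people still riding out of 20:

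| Still riding | % | 95% CI |
|---|---|---|
| 16/20 | 80 | 56 to 94 |
| 14/20 | 70 | 46 to 88 |
| 10/20 | 50 | 27 to 73 |
| 6/20 | 30 | 12 to 54 |

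Full attendance, 20/20, would read 100% (83% to 100%) beside any of these rows. Put the other way, 5 of 20 stopping is 25% (9% to 49%).

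**The case against.** The strongest case on the other side has several parts.

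- **Nobody is labelled adherent.** A reader might infer that a participant who stops riding is classed as adherent, or that the trial would announce full adherence. The document does not support that. It sets no threshold and classifies no one; it plans counts of attendance. This stands.
- **Riding is free.** With no target, low use breaches no instruction, and riding can fairly be called a behavioural outcome. This stands as far as it goes: there is no target to mis-score. It does not make attendance a measure of use.
- **Use is reported elsewhere.** Journeys, duration and distance appear under question 6. GPS and travel diary in the last intervention week include e-cycling as a transport mode. Observation checklists record whether behavioural skills are put into practice, and interviews explore barriers to riding. This stands, and it limits the harm. But the travel data are also summarised as mean and SD, and none of these sources is tied to question 2.
- **The list of primary outcomes is not closed.** It is worded as including the named items, so its silence on intervention adherence is weak evidence. Table 3 carries the point.
- **This is analysis-plan detail.** In part: median and IQR could be left to such a plan. But Table 3 itself names the indicator for question 2 and the summary for e-bike use, so the point concerns what is stated.
- **Weekly use is not known for everyone.** Watch or logbook use is encouraged only, and an odometer total neither dates the riding nor separates solo rides from instructor or group rides. This stands and shapes the fix.

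A reader might also infer that a wrong adherence figure would by itself decide whether a definitive trial goes ahead. The document has no progression rule on adherence, so that is not supported.

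**Conclusion.** The mismatch holds. A primary question on adherence to the intervention is answered in Table 3 by session attendance alone, and e-bike use is placed under a secondary question with a summary that cannot reveal non-riders or those who stopped. Attendance could look complete while use was low.

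The size cannot be predicted: the counts and distances above are illustrations, and the document gives no expected level of use. What is fixed is the resolution, 5 percentage points per person in an arm of 20, and the wide intervals that go with it. The conclusion rests on reading use of the loaned bike as part of adherence to the intervention, which is reasonable but not the only reading. Because use is reported elsewhere and no decision rule depends on adherence, this is an improvement worth making, not an error that undermines the trial.

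**What to change.** In Table 3, question 2, keep session attendance as its own line and add a separate descriptive line for e-bike use during the loan:

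- number and percentage of intervention participants with any recorded e-cycling outside instructor sessions;
- among those with watch or logbook data, number and percentage with a ride in the last weeks of the loan, the window being fixed in advance and the final-week GPS and diary used as a check;
- exact 95% confidence intervals for these proportions.

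Report total distance (odometer) and number of journeys as median, IQR and range beside the mean and SD. State how many participants have usable data for each item. Treat absent watch or logbook records as missing, not as no riding; where only an odometer total exists and it cannot be separated from session riding, treat the first item as missing too. Name adherence to the intervention in the primary-outcome sentence so that it agrees with question 2. None of this implies a riding target.

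The cost is wording in Table 3 and the analysis text; the data sources are already planned. The downsides are that the adherence picture may be less favourable, and that measures of when riding took place will be incomplete for participants with odometer data only.
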